##### Sample size estimation

We aim to enroll a total of 220 infants into the study. We assume 110 of these infants (50%) will receive RBC transfusion and undergo NIRS monitoring. Analysis comparing two groups, divided equally among infants by pIST, would provide more than 80% power to detect a difference of 10% in pre- and post-transfusion mean area under the curve MES-rSO_2_ change (standard deviation = 18) between groups or 90% power to detect a difference as small as 6% in MES-rSO_2_ with a standard deviation of 9 (Fig. 1 and Table 1). However, the number of infants enrolled in the study that receive a transfusion and have NIRS monitoring may be lower than 110. Therefore, we have provided power estimates for analysis of a sample size of 72 infants with RBC transfusion and NIRS monitoring (33% of the enrolled cohort). This will generate 80% power to detect a difference of 12% in pre- and post-transfusion mean area under the curve MES-rSO_2_ change between the two groups if the final sample size is 72 infants (36 per group) and the estimated standard deviation for MES-rSO_2_ change is 18. A secondary analysis evaluating pIST a continuous variable will also be performed, which will likely yield greater power for each of the scenarios presented.

**Table 1 Tab1:** Sample Size and Power Estimates

Groups	*n* = 220 transfused				*n* = 110 transfused				*n* = 72 transfused			
	SD = 9		SD = 18		SD = 9		SD = 18		SD = 9		SD = 18	
Difference in MES-rSO_2_ AUC change (%)	Effect Size	Power	Effect Size	Power	Effect Size	Power	Effect Size	Power	Effect Size	Power	Effect Size	Power
6	0.67	1	0.33	0.69	0.67	0.93	0.33	0.41				
8	0.89	1	0.44	0.91	0.89	1	0.44	0.64				
10	1.11	1	0.56	0.98	1.11	1	0.56	0.82	1.11	1	0.56	0.64
12	1.33	1	0.67	1	1.33	1	0.67	0.93	1.33	1	0.67	0.8

Abbreviations: *MES-rSO*_*2*_ mesenteric regional oxygen saturation, *AUC* area under curve, *SD* standard deviation

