### Primary outcome

All infants enrolled who receive RBC transfusion will have MES-rSO_2_ measured by NIRS as the primary study end-point [INVOS 5100C Cerebral/Somatic Oximeter (Covidien, Boulder, CO)], a Food and Drug Administration approved device for use on premature infants. NIRS noninvasively measures regional tissue saturation (rSO_2_) in real time because it calculates the difference between oxyhemoglobin (HbO_2_) and deoxyhemoglobin (HHb) expressed as: rSO_2_ = HbO_2_/HbO_2_ + HHb [47]. WE will obtain a baseline measurement by placing the NIRS probes on the infant at least 30 min prior to transfusion (triggered by the decision to transfuse made by the clinical team). Probes will remain in place to collect data for 48 h following transfusion completion. Two-probe site monitoring on mesenteric and renal beds will be used to evaluate differential tissue bed oxygenation. Adhesive sensor probes are vertically applied to left periumbilical area for mesenteric monitoring and horizontally to right flank for renal monitoring.

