### Statistical methods

We will use a novel statistical approach [51] implemented by the *NIRStat* R package for analyzing the NIRS data. Specifically, the *NIRStat* method models the observed MES-rSO_2_ time series with a nonparametric smooth function via penalized regression splines [49, 50]. It then provides accurate and robust statistical measures for characterizing the important features in rSO_2_ series. We will use the mean area under the fitted spline curves (MAUC) measure generated from the *NIRStat* package to measure the MES-rSO_2_ levels at baseline and then at post-transfusion. The MAUC changes from baseline to post-transfusion will be used to quantify the changes in MES-rSO_2_ due to transfusion. Two sample t-tests will be used to compare the changes in MAUC between saRBCs +/− pIST. Multivariate linear regression models will also be applied to model the changes in AUC in terms of pIST status (with pIST and without pIST) and other potential confounding factors. The multivariate analysis will allow us to assess whether the changes in MES-rSO_2_ differs significantly between saRBCs with pIST and those without pIST, controlling for other confounding factors.

The incidence of NEC and death will be estimated by the cumulative incidence function appropriate for competing risks. Gray’s method (modified log-rank test) will be used to compare NEC cumulative incidence according to baseline clinical characteristics. Cause-specific hazard ratios will be calculated to measure the degree of association between baseline characteristics and NEC, and between baseline characteristics and death by fitting a stratified Cox proportional-hazards regression model for competing risks. The competing risks model will be implemented using SAS PHREG using robust sandwich covariance matrix estimates to account for within-mother correlation that may occur in outcomes of multiple-birth infants.

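### Naming baseline MAUC as a covariate in the pIST comparison would probably gain precision at almost no cost; the planned t-test on raw change is valid but may give up power

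*Protocol article*

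**What the plan says.** The primary endpoint is the change in MES-rSO2 in response to transfusion. Statistical methods sets the outcome: "The MAUC changes from baseline to post-transfusion will be used to quantify the changes in MES-rSO_2_ due to transfusion". It then gives two analyses of that change.

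- The first is unadjusted: "Two sample t-tests will be used to compare the changes in MAUC between saRBCs" with and without pIST.
- The second is a regression: "Multivariate linear regression models will also be applied to model the changes in AUC in terms of pIST status" "and other potential confounding factors". The factors are not listed, and baseline MAUC is neither named nor excluded.

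Neither analysis is labelled primary, but the Sample size estimation section and Table 1 are built on the two-group comparison of change. For the fallback of 72 infants: "This will generate 80% power to detect a difference of 12" percent, with an SD of change of 18.

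The Primary outcome section shows that the baseline is available for each monitored transfusion. The team will "obtain a baseline measurement by placing the NIRS probes on the infant at least 30 min prior to transfusion", and afterwards "Probes will remain in place to collect data for 48 h following transfusion completion".

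**The concern.** A change score subtracts the whole baseline value, which fixes the slope of post-transfusion on baseline MAUC at 1. If the true slope differs from 1, the change carries baseline variation that a fitted covariate would remove. Baseline MAUC is measured before the unit is given, so that unit's pIST cannot have affected it, and it needs no new data collection.

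What is at stake is power. The article itself allows that the evaluable number may fall from 110 to 72 infants, where Table 1 gives only 0.64 power for a difference of 10 with SD 18.

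**Working it through.** **Inputs from the article (Sample size estimation, Table 1).** 55 per group (110 infants) or 36 per group (72 infants); SD of change 18; difference 10 or 12. Alpha and sidedness are not stated. Two-sided 0.05 is assumed because it reproduces Table 1; one-sided 0.05 does not (0.898 against 0.82 at 55 per group, normal approximation).

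**Inputs not in the article.** The correlation r between baseline and post-transfusion MAUC, and the ratio k of baseline SD to post SD. I assume r from 0.3 to 0.9 with k = 1, then vary k.

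**Step 1. Reproduce Table 1.** Noncentrality = difference / (SD × √(2/n per group)), two-sample t.

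- 55 per group, difference 10: 10 / (18 × √(2/55)) = 2.91, power 0.823 (Table 1: 0.82).
- 36 per group, difference 10: 10 / (18 × √(2/36)) = 2.36, power 0.642 (Table 1: 0.64).
- 36 per group, difference 12: 12 / (18 × √(2/36)) = 2.83, power 0.797 (Table 1: 0.80).

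**Step 2. Variance with baseline as a covariate.** With a common SD s, the change has variance 2s²(1 − r), and the residual after fitting baseline has variance s²(1 − r²). The ratio is (1 − r²) / [2(1 − r)] = (1 + r)/2. The adjusted SD is therefore 18 × √((1 + r)/2), with one degree of freedom removed.

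| Assumed r | Variance ratio | Adjusted SD | Power, 110 infants, difference 10 | Power, 72 infants, difference 10 |
|---|---|---|---|---|
| Change score, as planned | 1 | 18 | 0.82 | 0.64 |
| 0.3 | 0.65 | 14.51 | 0.95 | 0.82 |
| 0.5 | 0.75 | 15.59 | 0.92 | 0.77 |
| 0.7 | 0.85 | 16.60 | 0.88 | 0.71 |
| 0.9 | 0.95 | 17.54 | 0.84 | 0.66 |

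For 80% power at a difference of 10 (normal approximation), the number per group falls from 51 to 34, 39, 44 and 49 in the same order of r.

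**Step 3. Unequal SDs.** The ratio becomes (1 − r²) / (1 + k² − 2rk), and the slope is r/k.

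- k = 1.25, r = 0.5: 0.75 / 1.3125 = 0.571, slope 0.4. Power at 110 infants is 0.97.
- k = 0.8, r = 0.8: 0.36 / 0.36 = 1, slope 1. Power stays at 0.82, so there is no gain.

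These figures assume no baseline difference between the pIST groups. If baseline and pIST are correlated, the variance of the adjusted pIST coefficient is inflated and the gain shrinks.

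**Step 4. The endpoint is kept.** Because change = post − baseline, regressing either change or post value on pIST and baseline gives the same pIST coefficient and standard error. Only the baseline coefficient moves, by 1.

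**The case against.** The stated plan is valid. The t-test matches the declared endpoint, and Table 1 reproduces. The wording on potential confounders could admit baseline MAUC, and a condensed article may leave its covariate list to the analysis plan. The size of any gain rests on a correlation and an SD ratio that the article does not give. All of this stands, and it limits the point to an improvement rather than an error. What remains is that the article fixes and sizes an unadjusted comparison of raw change, and does not fix baseline as a covariate in the analysis beside it.

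A reader might infer two stronger claims.

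*That case mix biases the change score through regression to the mean, and that adjustment cures this.* The article does not support it: pIST is not randomised, and no baseline imbalance is reported. Take a true effect of 10, slope 0.5 and a baseline difference of 4 points between groups.

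- If the post value depends on the measured baseline, the change score estimates 10 − (1 − 0.5) × 4 = 8, and the adjusted model about 10.
- If the groups differ by a stable 4 points, post values differ by 14. The change score then gives 14 − 4 = 10, and the adjusted model 14 − 0.5 × 4 = 12.

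Simulation agrees (8.0 against 9.9, and 10.0 against 12.0). Which analysis is off depends on why the groups differ, which the article cannot tell us. Chance imbalance is already covered by the standard error of the change score.

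*That the slope must be well below 1 because a baseline of about 30 min is set against 48 h of post-transfusion recording.* A short, noisy baseline makes this plausible, but 30 min is a stated minimum and no slope is given.

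**Conclusion.** The point holds as a nearly free gain in precision, and only as that. With equal SDs, two-sided 0.05, no baseline difference between groups and r between 0.3 and 0.9, adjustment adds about 2 to 12 percentage points of power at 110 infants and about 2 to 18 at 72 (difference 10, SD 18). The gain is larger if baseline is the more variable measure, and nil if the slope is 1. Table 1 is correct for the test it describes; nothing in it needs correcting. A claim that the planned contrast is biased is not supported.

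**What to change.** In Statistical methods, name baseline MAUC as a prespecified covariate in the linear regression for pIST, both as two groups and as a continuous variable. Make that the main pIST analysis, and keep the two-sample t-test on change alongside it as a sensitivity analysis. Add a sentence saying that, because pIST is not randomised, the two can differ if baseline differs between pIST groups, and that neither is automatically unbiased. Table 1 can stay, described as the power of the unadjusted test; it should not be called conservative without qualification, since correlation between baseline and pIST could offset the gain.

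The cost is two sentences of analysis wording and one degree of freedom, with no new data and no change to the endpoint.

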##### Aims

The aims of this prospective, observational study are to (Fig. 1): 1) Determine the associations between RBC storage after irradiation (pIST), metabolic alterations in stored/irradiated RBCs, and changes in mesenteric digestive tract regional saturation of oxygen (MES-rSO_2_) measured by NIRS; 2) Compare in vitro measures of RBC function, and metabolic changes, between RBC products transfused to infants who develop NEC compared to matched control infants who do not; and 3) Explore the clinical implications of severe anemia (hemoglobin ≤8 g/dL) during the vulnerable “NEC window period” of 29–34 weeks postmenstrual age in the responses of infants < 1250 g to RBC transfusion. Our overarching hypothesis is that irradiation of RBC units followed by longer storage perturbs RBC metabolism and function leading to paradoxical microvascular constriction, mesenteric tissue hypoxia, and increased risk for NEC in transfused premature infants with already impaired intestinal oxygenation secondary to significant anemia.

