##### Study design

We will prospectively investigate, using an established birth cohort design [18, 46], the associations between RBC transfusion (including characteristics of transfused RBCs), anemia, intestinal oxygenation, and NEC. We specifically aim to understand the relationship between pIST, donor RBC metabolomics profiles, and recipient anemia on MES-rSO_2_, as measured by NIRS, and the development of NEC (Fig. 1). Although many studies have characterized the association between NEC and transfusion, none have focused on improving our understanding of the underlying pathophysiology, particularly the intestinal oxygenation changes preceding NEC. Further, the safety and efficacy of various blood banking practices including the preparation of storage-aged RBCs (saRBCs) and repeat donor exposure in recipients remains unclear. The safe threshold of saRBC+/− pIST in infants is not known and longer-stored saRBCs, either before or after irradiation, may potentiate the RBC storage lesion. This study may provide new knowledge regarding the potential benefit or harm of various blood banking practices and may identify new potential mediators of NEC.

The study schema (Fig. 1) illustrates how we aim to characterize the association between metabolic changes in transfused RBCs relative to pIST, and adverse effects in the recipient through two approaches: in vivo NIRS trend monitoring of intestinal oxygenation, and in vitro RBC functional studies. The schema explains how variables will be compared to evaluate primary and secondary endpoints for each specific aim. Our primary endpoint is changes in MES-rSO_2_ trends in response to transfusion of saRBC+/− pIST as measured by NIRS (Aim 1). Secondary endpoints are 1) to determine the hazard ratio of NEC comparing infants transfused with saRBCs with and without pIST; (2) examination of metabolomics fingerprints of transfused RBC (in vitro) among infants with and without NEC (Aim 2); and 3) impact of severity of anemia over time during the NEC window (29–34 weeks postmenstrual age) on MES-rSO_2_ (Aim 3).

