## Methods

All RBC transfusions given to infants during hospitalization will be studied. All RBC transfused units are stored in citrate-phosphate-dextrose-adenine (CPDA-1) preservative solution. pIST and storage days will be recorded for each RBC transfusion. All infants will be monitored with NIRS prior to, during and up to 48 h following each transfusion. Consistent with epidemiologic reports of transfusion-related NEC and prior studies at the 3 centers, we anticipate approximately 20 (10%) infants will develop NEC while on study. For our 2:1 case-controlled metabolomic analysis, we will prospectively analyze 40 infants who do not develop NEC and compare to 20 infants with NEC. Within this sub-cohort, we will compare alterations in metabolic pathways from saRBC unit (in vitro) and infant blood sample (in vivo). We will then examine a third sub-cohort of 120 infants without NEC within the NEC “window” (29–34 postmenstrual weeks’). These infants will also be monitored weekly for 24–48 h with mesenteric NIRS to evaluate the relationship between anemic (hemoglobin < 8 g/dL) and non-anemic infants. Reports suggest that this specific population of infants are more likely to experience paradoxical reductions in MES-rSO_2_ substantially increasing the risk for NEC when transfusions are given [10, 36]. Analysis will also include assessment of hemoglobin as a continuous variable.

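### The only pIST comparison with stated power is an unadjusted t-test, although pIST is not randomised and is part of the unit's total storage age; the planned regression should lead, with storage days and baseline MAUC fixed as covariates

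*Protocol article*

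**What the plan says.** All references are to the protocol article.

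- **Outcome.** Statistical methods: "We will use the mean area under the fitted spline curves (MAUC) measure", taken at baseline and after transfusion; the difference is the endpoint.
- **Group comparison.** Statistical methods: "Two sample t-tests will be used to compare the changes in MAUC between saRBCs" with and without pIST. Sample size estimation gives power for two equal pIST groups. Continuous pIST is a secondary analysis.
- **Adjusted model.** Statistical methods: "Multivariate linear regression models will also be applied to model the changes in AUC in terms of pIST status (with pIST and without pIST", with confounders added. The stated purpose is to test the pIST difference "controlling for other confounding factors". No confounder is named.
- **Exposure.** Background and Aims define pIST as storage time after irradiation. Study design says that "longer-stored saRBCs, either before or after irradiation, may potentiate the RBC storage lesion".
- **Data.** Methods: "pIST and storage days will be recorded for each RBC transfusion".
- **Recording.** At least 30 minutes before transfusion and then, under Primary outcome, "Probes will remain in place to collect data for 48 h following transfusion completion".

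**The concern.** The cohort is observational, so nothing balances the two pIST groups. Total storage age equals storage before irradiation plus pIST. If the groups also differ in unit age, an unadjusted difference in MAUC change mixes the two. The article cannot treat unit age as irrelevant: it names storage before irradiation as a possible cause of the same lesion. Its Background remark that storage age has not been shown to raise NEC risk concerns NEC, not mesenteric saturation.

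At stake is the interpretation of the primary endpoint. A positive t-test could reflect older units, and a null one could hide a pIST effect if long-pIST units happened to be irradiated early. Recipient anemia is a second candidate, since the hypothesis concerns effects "in transfused premature infants with already impaired intestinal oxygenation secondary to significant anemia".

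**Working it through.** **1. Which analysis the stated power describes.** Inputs from Sample size estimation and Table 1: difference d, SD s, n per group. Two-sided alpha of 0.05 is assumed, because the article states none. The noncentrality is d / (s × √(2/n)), and power comes from the noncentral t distribution.

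| Scenario | Noncentrality | Computed power | Table 1 |
|---|---|---|---|
| d = 10, s = 18, 55 per group | 10 / (18 × 0.1907) = 2.91 | 0.823 | 0.82 |
| d = 6, s = 9, 55 per group | 6 / (9 × 0.1907) = 3.50 | 0.934 | 0.93 |
| d = 12, s = 18, 36 per group | 12 / (18 × 0.2357) = 2.83 | 0.797 | 0.80 |

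All 20 filled power cells reproduce within 2 points by the normal approximation. The stated power is that of an unadjusted two-sample comparison.

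**2. Which storage covariate separates the two.** Suppose the outcome is b × total + g × pIST, where b is ordinary ageing per day and g is the extra effect of time spent irradiated. Since total = pre + pIST, this equals b × pre + (b + g) × pIST. Adjusting for pre-irradiation days leaves b inside the pIST coefficient. Adjusting for total storage days leaves g alone, the effect of post-irradiation time at a given unit age.

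**3. Possible bias of the unadjusted test (illustration).** The article gives neither the storage slope nor the storage gap between groups. Assume 0.25 to 1.0 point per day and a gap of 3 to 7 days. Bias = slope × gap, from 0.25 × 3 = 0.75 to 1.0 × 7 = 7 points. With no pIST effect and 55 per group, the false-positive rate is 5.5% to 52% at SD 18 and 7% to 98% at SD 9, against a nominal 5%.

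**4. Cost of adjusting for storage.** Let r be the correlation of pIST status with total storage days. The variance of the pIST coefficient is multiplied by 1/(1 − r²). The article gives no r, so a range is assumed; the residual SD is unchanged and one further degree of freedom is spent.

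| r | Variance factor | d = 10, SD 18, n = 110 | d = 6, SD 9, n = 110 | d = 12, SD 18, n = 72 |
|---|---|---|---|---|
| 0 | 1.00 | 0.82 | 0.93 | 0.80 |
| 0.3 | 1.10 | 0.79 | 0.91 | 0.76 |
| 0.5 | 1.33 | 0.71 | 0.85 | 0.68 |
| 0.7 | 1.96 | 0.54 | 0.70 | 0.51 |
| 0.9 | 5.26 | 0.24 | 0.33 | 0.23 |

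**5. Gain from baseline adjustment.** With equal baseline and post-transfusion variances and correlation ρ, residual variance relative to the change score is (1 − ρ²) / (2(1 − ρ)) = (1 + ρ)/2, which is 0.75 at ρ = 0.5 and 0.85 at ρ = 0.7. If baseline MAUC is unrelated to pIST and storage, the factors multiply: at r = 0.5 and ρ = 0.5, 1.33 × 0.75 = 1.00, so the loss is recovered; at r = 0.7, 1.96 × 0.75 = 1.47, so it is not. The article gives no ρ, and equal variances are doubtful for a window of about 30 minutes against 48 hours.

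**6. The word AUC in the regression sentence.** At an assumed constant saturation of 50%, a raw area is 50 × 0.5 = 25 %·h before transfusion and 50 × 48 = 2,400 %·h after, a difference of 2,375 with no physiological change. The mean-area change is 0. Table 1 works in differences of 6 to 12%, which fits only the mean area.

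**The case against.** The strongest reply is that confounding is already provided for. The article plans a regression for this purpose, storage days are available to it, and a covariate list may sit in a full protocol or SAP that is not shown. Nor does the article call the t-test primary; that is inferred from its being listed first and carrying the power. This reply stands against a reader who infers that neither analysis isolates pIST: the regression can, if storage age is in it. It does not rescue the t-test, and it leaves the only powered analysis as the one that cannot answer the question.

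A reader might also infer that the regression uses a raw area that grows with recording length. The article does not support this. The same paragraph sets MAUC as the measure, and Table 1 labels as AUC change what the text calls mean area under the curve. It is a wording slip.

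Three further objections hold in part:

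- The bias figures are assumptions. A gap in total storage may consist largely of pIST itself, and long-pIST units need not be older overall.
- A change score is not an error. In non-randomised groups, change scores and baseline adjustment rest on different assumptions about baseline differences. The case for adjustment is that its residual variance is never larger and that baseline imbalance is dealt with openly.
- The hypothesis refers to anemic infants, but the primary endpoint is not conditional on anemia, which has its own aim. A pIST-by-hemoglobin interaction is therefore optional.

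**Conclusion.** The point holds in this form: the only pIST comparison with stated power is an unadjusted t-test on MAUC change for a non-randomised exposure that is arithmetically part of a recorded rival exposure. A regression is planned, but it does not lead, and storage age and baseline MAUC are not fixed in it.

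The lost precision is the firmer figure, conditional on r: power of 0.82 becomes about 0.79, 0.71 or 0.54 at r = 0.3, 0.5 or 0.7, before any gain from baseline adjustment. The 0.75 to 7 points of bias show only that a problem of the size of the target effect is possible; the documents do not establish that it will occur. Both rest on two-sided alpha of 0.05 and on assumed values of r, slope and gap.

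**What to change.** In Statistical methods:

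- Name the adjusted linear regression as the main pIST analysis, and write MAUC throughout.
- Fix as covariates baseline MAUC, total storage days and pre-transfusion hemoglobin. State that the pIST coefficient is then the effect of post-irradiation time at a given unit age.
- Keep the two-sample t-test as descriptive.

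In Sample size estimation, restate power for this model over a range of pIST-storage correlations, or with the correlation observed in the centres' own transfusion records if available.

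The cost is wording and one power calculation. Storage days and baseline MAUC are already collected. Hemoglobin is already planned for analysis, but the article does not say that a value is taken shortly before each transfusion, so this should be confirmed. The real price is precision: if pIST and storage age are strongly correlated the interval will be wide, and the report should say so.

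### The hypothesis ties the harm of long post-irradiation storage to anemic infants, but no stated analysis examines the pIST effect by anemia

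*Protocol article*

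**What the plan says.** **Hypothesis.** The Aims section expects "increased risk for NEC in transfused premature infants with already impaired intestinal oxygenation secondary to significant anemia". The Abstract and the Discussion restate this. The background section on the storage lesion describes stored cells and immature endothelium acting together in a preterm infant with anemia. The Methods section adds that the anemic population is the one more likely to show paradoxical falls in MES-rSO2 when transfused.

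**pIST analyses.** Under Statistical methods, "Two sample t-tests will be used to compare the changes in MAUC between saRBCs" with and without pIST. Regression will then "model the changes in AUC in terms of pIST status (with pIST and without pIST) and other potential confounding factors", and its declared purpose is to see whether the change differs by pIST after adjustment. The Sample size section and Table 1 power only this two-group contrast, with infants "divided equally among infants by pIST".

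**Anemia analyses.** Aim 3 explores severe anemia (hemoglobin ≤8 g/dL) at 29–34 weeks "in the responses of infants < 1250 g to RBC transfusion". Study design lists severity of anemia and MES-rSO2 as a secondary endpoint. The Methods section describes 120 infants without NEC who will also be "monitored weekly for 24–48 h with mesenteric NIRS to evaluate the relationship between anemic" and non-anemic infants, with hemoglobin analysed as a continuous variable too. None of these statements mentions pIST.

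**The concern.** The hypothesis is one of effect modification: pIST should matter more, or mainly, in infants who are already anemic. A t-test by pIST and a regression on pIST plus confounders both estimate a single pIST effect averaged over all transfused infants. Entering hemoglobin as a confounder would not change that, because adjustment still assumes a common pIST effect at every hemoglobin level.

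Two consequences follow. An average close to zero could not be read as evidence against the hypothesis, since it might conceal an effect in the infants of interest. And a pIST comparison within anemic infants, made after a null average result, would be an unplanned subgroup finding with little credibility, although the data for a planned one are already to be collected.

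**Working it through.** **Inputs from the article.** Analysed sample: "We assume 110 of these infants (50%) will receive RBC transfusion and undergo NIRS monitoring", so 55 per group; the fallback is "if the final sample size is 72 infants (36 per group"). Difference 10 with SD 18, or 6 with SD 9, at 110 infants; difference 12 with SD 18 at 72. The test is a two-sample t-test.

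**Assumptions.** Two-sided 5% level (not stated, but it reproduces Table 1). One change score per infant. The same anemic share p in both pIST groups. The article does not give p, so a range is shown.

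**Step 1: reproduce the plan.** SE of the average contrast = SD × √(4/N) = 18 × √(4/110) = 3.43. Noncentrality = 10/3.43 = 2.91, and with 108 degrees of freedom power is 0.823 (Table 1: 0.82). Difference 6, SD 9, N = 110 gives 0.934 (0.93). Difference 12, SD 18, N = 72 gives 0.797 (0.80). Table 1 is correct for a uniform effect.

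**Step 2: effect in anemic infants only.** The average difference becomes p × d.

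| Share p | Power, N=110, d=10, SD 18 | Power, N=72, d=12, SD 18 | Power, N=110, d=6, SD 9 |
|---|---|---|---|
| 20% | 9% | 9% | 11% |
| 50% | 30% | 29% | 41% |
| 75% | 58% | 55% | 74% |
| 90% | 74% | 71% | 88% |
| 100% | 82% | 80% | 93% |

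In the three scenarios power falls below 50% when p is under about 0.68, 0.70 and 0.57 respectively.

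**Step 3: half the effect in non-anemic infants.** The average is d(1 + p)/2. With N = 110, d = 10, SD 18 and p = 50% this is 7.5 points, and power is 58% rather than 30%.

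**Step 4: what an added analysis can deliver (N = 110, d = 10, SD 18, effect in anemic infants only).**
- *pIST contrast within the anemic stratum.* SE = SD × √(4/(Np)), with N − 4 degrees of freedom. Power is 25%, 35%, 45% and 53% for shares of 20%, 30%, 40% and 50%. The 95% CI half-width is about 1.98 × 18 × √(4/22) = 15.2 points at 20% and 1.98 × 18 × √(4/55) = 9.6 points at 50%.
- *Interaction test.* SE = SD × √(4/(Np) + 4/(N(1 − p))). Power is 24%, 30% and 24% for shares of 25%, 50% and 75%.
- *Continuous hemoglobin model read at the cut-off.* Simulated with normally distributed hemoglobin (an assumption) and a true step at the cut-off. Power is about 15–16%, 21–23% and 28–30% for shares of 20%, 30% and 50%. The linear term recovers only about 4 to 5 of the 10 points.

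**The case against.** **The primary analysis matches its own aim.** Aim 1 and the primary endpoint ask about pIST and MES-rSO2, without conditioning on anemia. This stands, and it is why the average effect should remain primary. It does not supply a test of the overarching hypothesis.

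**A condensed article may leave interaction terms to the SAP.** A detail left out would not be a finding. Here, however, the article states the regression and its purpose, and both leave out the condition on which the hypothesis rests.

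**A reader might infer that the effect will probably be missed.** The article does not support that. Every infant in the primary analysis is transfused, and the Background says transfusion is mostly given for anemia of prematurity. Under a broad reading of significant anemia the share could be high and the dilution modest; at Aim 3's cut-off for severe anemia it could be small.

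**A reader might infer that an anemia-specific analysis is always more powerful than the planned test.** That requires no effect at all in non-anemic infants, which the article never asserts. Its language of synergy and exacerbation also fits an effect that is merely larger in anemic infants. If non-anemic infants have half the effect, the planned test is at least as powerful at every share, because (1 + p)/2 ≥ √p. At shares of 20%, 30%, 40% and 50% it has 41%, 47%, 52% and 58% power, against 25%, 35%, 45% and 53% for the stratum contrast.

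**A reader might infer that Aim 3 cannot answer its own question because its recordings are weekly.** The Methods section says these infants are also monitored weekly, on top of monitoring around every transfusion. The transfusion recordings exist and nothing bars their use. What is missing is a statement that Aim 3 uses them.

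**Conclusion.** The concern holds as a mismatch between hypothesis and stated analysis. The hypothesis is conditional on anemia, the pIST analyses are not, and the anemia analyses omit pIST.

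The possible loss of power in the average test runs from slight to severe: from 82% to 74% if 90% of analysed infants are anemic, and to 9% if 20% are (10 points in anemic infants only, SD 18, 110 infants). The size rests on three things the article does not settle: the anemic share, the effect in non-anemic infants, and which of its two SDs applies. Table 1 itself contains no error. The point warrants a change to the plan as a secondary analysis; it does not call for replacing the primary one.

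**What to change.** 1. Keep the average pIST effect as the primary result.
2. In the Statistical methods regression, prespecify as a secondary analysis pre-transfusion hemoglobin and a pIST by hemoglobin product term. Name it as the analysis that addresses the overarching hypothesis.
3. Report the pIST effect with 95% CI in anemic and in non-anemic infants, using the protocol's own 8 g/dL cut-off. Give it both as a stratum contrast and from the continuous model, because a linear term understates a step at the cut-off. The Aims section defines the cut-off as ≤8 and the Methods section as <8; the two must be reconciled before the stratum is fixed.
4. State the expected share of anemic infants among those transfused, with the power or expected interval width that follows.
5. State that Aim 3's question on response to transfusion uses the transfusion NIRS recordings already collected at 29–34 weeks, as well as the weekly recordings.

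**Cost.** One covariate, one product term, a few lines of text and no new monitoring. The downside is one more secondary estimate, with a wide interval at SD 18. Label it as estimation and not as a powered test.
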